#### Secondary outcomes

##### Child non-core food intake

Absolute changes in child intake of non-core foods will be assessed based on the scores on the non-core foods subscale of the CDQ [54].

##### Child weight status

Child BMI percentile will be assessed based on parent-reported child height (m) and weight (kg) using standard items from the NSW Population Health Survey, which have been tested for reliability and convergent validity [56, 57].

##### Child physical activity and sedentary screen-time

Child physical activity will be assessed using a parent-reported questionnaire. Parents will be asked about the amount of time (in minutes) that their child was physically active during the whole day prior to the interview and specifically how much of this was of moderate or vigorous intensity. They will also be asked how many days over the past week their child was active for at least 3 hours. Parents will be asked about the amount of time (in minutes) that their child used electronic media devices (including TV, consoles and hand-held devices) while sitting or lying down during the whole day prior to the interview. They will also be asked how many days over the past week their child used such electronic media devices for less than 1 hour. These questions were modified from the National Nutrition and Physical Activity Survey (Australian Bureau of Statistics 2011) and are intended to assess compliance to the physical activity and screen-time components of the Australian 24-h Movement Guidelines for the Early Years. Compared with accelerometer measures, correlations between parent-reported measures of the percentage of time in sedentary, moderate, vigorous and moderate- to vigorous-intensity activity ranged from *r* = 0.35 to 0.49 [58] and it is therefore considered acceptable to use parent-reported data to assess physical activity and sedentary time.

##### Child sleep

The modified Children’s Sleep Habits Questionnaire will be used to assess child sleep duration and nap time and compliance with the sleep component of the Australian 24-h Movement Guidelines for the Early Years. The questionnaire items will also assess sleep reluctance. The questionnaire has been validated against accelerometry in samples that included preschool-aged children [59].

##### Mediators

Selected factors identified as key potential/hypothesised mediators of the interventions will be assessed, drawn from items in the Healthy Home Survey (HHS) [60]. These include the following: fruit and vegetable availability (i.e. available from the home environment), fruit and vegetable accessibility (i.e. able to be accessed in home environment - fruit and vegetables are within reach in ready to eat form), providing behaviour of parents, and family mealtime practices (family eating dinner at table together, not watching TV while eating a meal). These items were previously identified as potential mediators in the *Healthy Habits* efficacy trial [61].

##### Cost and cost effectiveness

Alongside relative study effects on primary (fruit and vegetable) and secondary outcomes (non-core food, physical activity, sleep, screen time and sedentary behaviours) information about resource use and costs will be collected from intervention and comparison arms. Resource use and costs of strategies across arms include staff time and capital costs originating at program, community and individual level. Staff time covers recruitment of participants, arrangement and delivery of the interventions (telephone interviewer and Facebook group facilitator time and program administration) costed at the relevant wage rates (including penalty rates and on-costs). Within trial relative costs of alternative strategies over 9-month follow-up will be estimated from observed resources used in implementation at a participant and local health district level applying relevant prices**.** Population level joint distribution of cost and effects under uncertainty will be jointly considered under uncertainty employing bootstrapping at individual and local health district level in net benefit assessment. This approach allows robust estimation of within study joint distribution under uncertainty of the relationship (covariance) between costs and effects observed in the randomised population [62].

Longer term effects and costs of strategies will be estimated triangulating across trial evidence of individual and community uptake, dose and effects from population exposure, indication of strategy continuation beyond trial, and wider community uptake of strategies. Triangulation of evidence is key to satisfy comparability and coverage in robustly informing societal decision makers of the relative net benefit of strategies under uncertainty in evaluating the effectiveness and cost effectiveness of health promotion interventions [63–65].

##### Participant preference

One of the objectives of the study is to determine the preferred user delivery medium. This will be assessed two ways. Ex-ante preferences will be determined at the conclusion of baseline data collection, where participants will be asked if they have a strong preference in regard to the way that they receive information and if so, what their preferred medium is (telephone, online or written materials). Ex-post preferences will be determined at the conclusion of the 3-month follow-up, where all participants will be asked whether they would have preferred for the information to be delivered by a different mechanism. They will be provided with the following options; telephone counselling, online program, educational materials, smartphone app, face-to-face, Skype, or other.

##### Comparison of recruitment & retention strategies

Several recruitment strategies will be employed by Local Health District staff at a local level and other broad-level recruitment strategies will also be applied (refer to recruitment section for details). Local Health Districts will decide which of these strategies to employ depending on their capacity and/or existing relationships with agencies and the community. To determine the most successful strategies, participants will be asked a multiple-choice question about how they found out about the program at the baseline data collection interview. These data will also be used to determine if there are recruitment strategies which are associated with a higher retention rate. A standard spreadsheet will also be used by each Local Health District to capture data on face-to-face recruitment initiatives, detailing the number of sites attended, number of parents approached, and number providing consent which will assist in determining which face-to-face sites are most successful for recruiting participants to the study.

##### Fidelity of interventions

The delivery of the interventions will be monitored and the data used to determine if the interventions were delivered as intended. Number of scheduled calls completed will be used to measure the fidelity of the *Healthy Habits Plus* intervention. Number of modules completed will be used to measure the fidelity of the *Time2bHealthy* online intervention. Number of emails/mailouts sent will be used to measure the fidelity of the comparison (written) intervention.

### Participant timeline

There are three scheduled assessment time-points; baseline, 3-month (immediately post-intervention) and 9-month post baseline follow-up (approximately 6-months post-intervention). Participants will receive a phone call at the baseline and 9-month time-points. Data will be collected by trained telephone interviewers using Computer Assisted Telephone Interviewing (CATI). The questionnaire comprises questions as described in the outcome measures. At 9-month follow-up, data collectors will be blinded to the study arm that the participants are assigned to. To maximise retention, up to 15 attempted calls will be made to participants at baseline and follow-up, leaving a voice message at the first opportunity. These calls will be complemented by an SMS after the 4th and 9th call attempt. The SMS after the 9th call attempt will ask participants if they would like to participate (Y or N). If they respond ‘N’, they will be withdrawn from the study.

The 3-month post-baseline assessment will include primary and secondary child behavioural outcome measure questions repeated from the baseline questionnaire, as well as a brief process evaluation. This will be completed either over the phone (for *Healthy Habits Plus* participants), online (for *Time2bHealthy* participants) or via mail/email (for comparison participants). The process evaluation will assess the user acceptance of the content and modality of each of the programs. The outcomes questions will include the fruit and vegetable subscale of the CDQ, and servings-based questions about fruit and vegetable intake (primary outcome). in addition to questions relating to the child’s physical activity, screen-time and sleep over the previous 24-h period (secondary outcomes). Figure 1 outlines the data collection time points and Fig. 2 provides an overview of the schedule of enrolment, interventions and assessments.

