### Eligibility criteria

Parents will be eligible if they live in New South Wales, have a child 2–6 years of age at the time of the baseline interview, live with the child at least 4 days on an average week, have access to telephone and internet, and understand and speak English sufficiently to participate. Parents will be excluded if they have previously participated in the *Time2bHealthy* or *Healthy Habits* randomised controlled trials (RCTs).

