### Study design, sample size and study power

For the primary analysis, sample size calculations for the randomised population are based on detecting between group differences in the proportion of randomised children with fruit and vegetable intake patterns consistent with dietary guidelines, as determined by a score of 14 or more on the fruit and vegetable subscale of the CDQ [54], the primary outcome alone. Accounting for 20% attrition, 117 randomised participants per arm (351 in total) are needed to complete baseline data collection with adequate power, resulting in a sample size of 93 participants per group at the 9-month post- baseline follow-up. For 80% power at a 0.05 significance level, this will allow a 20% detectable difference between intervention and comparison groups in adherence to dietary guideline recommendations assessed using the CDQ fruit and vegetable subscale. The overall sample size of 636 participants was based on a more conservative effect size estimate of 15%.

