The study has a number of strengths. The coverage of effects and their duration across major lifestyle factors for obesity prevention (physical activity, sedentary behaviour and sleep and their combinations alongside diet) and the novel partially randomised preference trial design of the study offers advantages in enabling synthesis of preference and RCT evidence. Adequate coverage of duration and scope of effects is particularly important for a pragmatic trial aimed at robustly informing societal decision and policy making of the population level effectiveness and cost effectiveness of alternative health promotion strategies in community settings (Eckermann and McCaffrey 2017; McCaffery and Eckermann 2017; Sheill et al. 1995, 2008, 2018). In health promotion settings preference based design also has potential for some advantages of internal and external validity over traditional RCTs, given potential participants may decline to enrol in RCTs if they have a strong preference for study arm and do not want to be randomised into their non-preferred arm. The absence of these potential participants in trials can affect the external validity of the study as the sample is unlikely to be representative of the population and therefore generalisability of the study can be affected [44]. Furthermore, internal validity of such trials can be affected by participants who do choose to be randomised but are allocated to their non-preferred arm. Such participants may be less likely to be motivated to actively participate and/or follow the intervention through to completion [44].

Other strengths include the blinding of telephone data collectors (outcome assessors), and the accessibility of the study to all residents of NSW, regardless of geographic location. As all data are collected via telephone or online and the interventions are delivered by telephone, online or email/mail and no face-to-face contact is required, usual barriers to traditionally delivered studies such as travel, scheduling of appointments and childcare for other siblings are not applicable. Accessibility of the study in rural and remote areas is particularly important given the higher prevalence of overweight and obesity and limited services in many areas [68].

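### At 3 months the outcome items are collected by a different mode in each arm, so the 3-month arm contrasts cannot be separated from mode of measurement

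*Protocol article*

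**What the plan says.** All of the collection details are in the Protocol article, Participant timeline.

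- Baseline and 9 months: "Participants will receive a phone call at the baseline and 9-month time-points". Both use computer-assisted telephone interviewing, whatever the arm.
- 3 months, content: "The 3-month post-baseline assessment will include primary and secondary child behavioural outcome measure questions repeated from the baseline questionnaire", together with a brief process evaluation. The primary outcome is named explicitly: "The outcomes questions will include the fruit and vegetable subscale of the CDQ, and servings-based questions about fruit and vegetable intake (primary outcome").
- 3 months, mode: "This will be completed either over the phone (for *Healthy Habits Plus* participants), online (for *Time2bHealthy* participants) or via mail/email (for comparison participants").
- Blinding: "At 9-month follow-up, data collectors will be blinded to the study arm that the participants are assigned to". Nothing comparable is said for 3 months.

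Elsewhere, the Discussion lists blinding as a strength with no time-point: "Other strengths include the blinding of telephone data collectors (outcome assessors"). The sample size section fixes the analysed number at the later visit: "resulting in a sample size of 93 participants per group at the 9-month post- baseline follow-up". Statistical methods (Impact of intervention) allows generalised estimating equations or mixed models for the primary outcome, names no primary time-point and does not mention mode. Eligibility criteria require that parents "have access to telephone and internet".

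**The concern.** The outcome is reported by the parent, and a parent may answer an interviewer differently from a form. In most trials that matters little, because every arm is measured in the same way. Here the telephone arm stays with a live interviewer at 3 months, while the other two arms move from interview to self-completion. Any effect of that move on reported intake appears in the 3-month results as a difference between programmes.

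At stake is the 3-month comparison of all three arms on the primary outcome and on the movement and sleep outcomes. The main result is at stake only if the 3-month values are combined with the 9-month values into one treatment effect.

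**Working it through.** **1. Does the arm-specific mode apply to the outcome items?** Yes. The sentence assigning the modes refers back to the whole 3-month assessment. The sentence that introduces that assessment lists primary and secondary outcome questions, and a later one names the fruit and vegetable subscale and the servings questions. The arm-specific mode is not confined to the process evaluation.

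**2. What each contrast estimates.** Write the reported value as the true value plus a mode term: *m_tel*, *m_web* or *m_mail* (mail or email). Let *d_H*, *d_T* and *d_C* be the true changes from baseline in Healthy Habits Plus, Time2bHealthy and comparison. Baseline carries *m_tel* in every arm, so the reported changes at 3 months are:

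- Healthy Habits Plus: *d_H*
- Time2bHealthy: *d_T* + (*m_web* − *m_tel*)
- Comparison: *d_C* + (*m_mail* − *m_tel*)

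The contrasts are:

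- Telephone v comparison: (*d_H* − *d_C*) + (*m_tel* − *m_mail*)
- Telephone v online: (*d_H* − *d_T*) + (*m_tel* − *m_web*)
- Online v comparison: (*d_T* − *d_C*) + (*m_web* − *m_mail*)

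No mode is shared by two arms at 3 months and baseline has only one mode, so the mode terms cannot be estimated. Baseline adjustment does not help. Adding the preference participants does not help either, because no different mode is given for them. At 9 months every arm carries *m_tel*, and it cancels.

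**3. The protocol's own figure.** Inputs from the sample size section: 20-point difference, 80% power, alpha 0.05 (two-tailed, from Statistical methods), 20% attrition. The comparison-group proportion is not stated; 0.30 is assumed.

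n = [1.960 × √(2 × 0.40 × 0.60) + 0.842 × √(0.30 × 0.70 + 0.50 × 0.50)]² / 0.20² = (1.358 + 0.571)² / 0.04 = 93.0, that is 93 per arm.

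93 / 0.80 = 116.25, rounded up to 117; 3 × 117 = 351. The stated figures reproduce.

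**4. What an assumed mode shift would do at 3 months.** The protocol gives no size for a mode effect, so this is an illustration only. It takes 93 analysed per arm, a comparison proportion of 0.30 to 0.50, and the same two-proportion normal approximation. The shift *b* is in percentage points of children scoring 14 or more.

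| Assumed shift *b* | Bias in a 3-month telephone contrast | Rejection rate with no true effect | Power for a true 20-point effect if *b* runs against it |
|---|---|---|---|
| 0 | 0 | 0.05 | 0.78–0.80 |
| 3 | 3 | about 0.07 | 0.64–0.67 |
| 5 | 5 | about 0.11 | 0.54–0.56 |
| 10 | 10 | 0.28–0.30 | 0.28–0.30 |

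A 10-point shift is 10/20, or half, of the detectable difference.

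**5. When would this reach the main result?** If one effect is pooled with weight *w* on 3 months, the pooled estimate carries *w* × *b*. At equal weights that is 5 × 0.5 = 2.5 points, or 10 × 0.5 = 5 points. If the model has arm-by-time terms, a constant shift in one arm at 3 months is taken up by that arm's 3-month mean. In a linear model the residuals are then unchanged, and so is the 9-month contrast. A mode effect that varies between parents, or a logistic model with dropout, need not cancel exactly.

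**The case against.** The strongest reply is that the comparison that matters is sound. The sample size is set at 9 months, where all arms are interviewed by telephone and the interviewers are blinded. That stands, and it confines the defect to an intermediate visit.

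A reader might infer that any repeated-measures model containing the 3-month values biases the main result. The protocol does not support that. It holds only if a single effect is pooled over both visits; Statistical methods does not say that it will be, and the time structure of the model is commonly left to the analysis plan. What remains is that no sentence names 9 months as the primary time-point, so pooling is not excluded.

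A reader might also infer that an interviewer effect distorts all three contrasts alike, or that response will differ by mode. The first is wrong: online and comparison are both self-completed, so only a web versus mail or email difference separates them. The second is possible but not established by the protocol.

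On blinding, the Discussion speaks only of telephone data collectors. The baseline interview precedes allocation, the 9-month interview is blinded, and two arms have no interviewer at 3 months. The statement is therefore not shown to be false, only broader than Participant timeline supports. Because only Healthy Habits Plus parents are telephoned at 3 months, the call itself reveals the arm.

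Acceptability and ex-post preference are also collected around this contact. Mode could colour the answers, but the protocol does not plan them as treatment-effect contrasts.

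**Conclusion.** The point holds for the 3-month contrasts. Arm and mode coincide, so those contrasts cannot be read as programme effects, and no later analysis can repair this. The exposure is greatest for telephone against either other arm, and less for online against comparison.

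The size is unknown. The 0 to 10 point range is an assumption, and so is the use of 93 analysed per arm at 3 months. Direction is unknown too: the bias could create an apparent effect or hide a real one.

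The 9-month contrast stands, provided that 3 and 9 months are not pooled into one effect. This should be fixed, but it does not undermine the powered comparison.

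**What to change.** 1. Collect the 3-month outcome items with one web form and one reminder schedule in all arms. Internet access is already an eligibility criterion. Keep only the programme-specific process questions in the arm's own medium. Cost: one shared form, and possibly lower 3-month response in the telephone arm than an interviewer call would give. If 3-month collection has begun, it also needs a protocol amendment, and the 3-month data would be split between two procedures.
2. State that the primary effect is the 9-month telephone-interview contrast, estimated either from baseline and 9-month data or from a model with arm-by-time terms that does not pool the two follow-ups. Report any 3-month contrast collected by mixed mode as confounded with mode. Cost: a few lines of text. This step is worth taking even if step 1 is no longer practicable.
3. Limit the blinding statement in the Discussion to the 9-month data collectors, as Participant timeline does. Cost: one clause.

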**Fig. 1 Fig1:**
[figure not shown]
Study Flow Chart (prior to application of the stopping rule)

**Fig. 2 Fig2:**
[figure not shown]
Time for Healthy Habits study schedule of enrolment, interventions, and assessments

### Recruitment

A recruitment strategy was developed by the Project Steering Committee in consultation with the Participant Recruitment Working Group, consisting of key stakeholders from the NSW Office of Preventive Health, the University of Wollongong, the University of Newcastle and the Population Health division of each of the Local Health Districts participating in the study.

Each Local Health District has been actively involved in the recruitment planning process and in addition to the main aims of the study, the project also presents an opportunity to help to build research capacity in Local Health District health promotion staff. Each Local Health District will appoint a Recruitment Officer who will be responsible for recruitment in their local area, supported by a central Project Coordinator. The Recruitment Officers will conduct face-to-face visits to locations such as Early Childhood Education and Care Services, playgroups, clinics and early childhood activities to promote and discuss the study with parents and provide them with participant information sheets and consent forms, or give them the option to sign up to the study electronically. Recruitment officers will also discuss the study with health professionals in their area and ask them to refer any suitable parents to the study. Flyers and/or information sheets and consent forms will be provided to local health professionals to offer to patients. Promotional materials will also be provided to other key stakeholders in the local area and information will be communicated via local newsletters, community noticeboards, media releases, social media, and local networks. The study will also be promoted through a media release to local media outlets and to parenting groups on Facebook.

Parents will gain information and provide informed consent either through hard copy participant information sheets and consent forms provided by the Recruitment Officer or Project Coordinator or online through the study website https://timeforhealthyhabitsnsw.com

